#### Discomfort reported by participants

The participant will be questioned about the discomfort related to the intervention immediately after the treatment is finished using the Face Image Scale (FIS) [14]. The scale will be shown to the children and they will be asked to point to the image that represents their discomfort level after the question: how do you feel at this moment? Without the operator’s presence, the dental assistant will ask for the participant’s most honest opinion.

#### Satisfaction of the participants

The treatment satisfaction of the participants will be rated using a close-ended questionnaire six months from the initial treatment. To each question, the participants will be asked to point the image that represents their feelings. The FIS scale will be used as explained above.

#### Perception of the parents/legal guardians

The perception of the parents or guardians concerning the treatment will be evaluated by the "Child's and parent's questionnaire about teeth appearance" [15] applied before the treatment, immediately after, and six months later. The dental assistant alone will ask for their honest opinion.

### Data analysis

The efficacy of each treatment will be evaluated according to five main outcomes:Tooth survival (primary outcome): The outcome will be dichotomized as survival versus failure. Kaplan Meier’s plot with overall survival in intention-to-treat (ITT) study population will be performed. The ITT study population will include all randomized participants regardless of protocol deviations, non‐compliance, or early study withdrawal. The Log-Rank test will be used to compare the survival curves of the two groups. The multivariate Cox regression with shared frailty model will be used to evaluate the influence of the explanatory variables (sex, age, jaw, type of teeth, toothbrushing, use of fluoride toothpaste, and dental floss) on the outcome. Hazard ratios (HR) with the respective 95% confidence interval will be calculated.Cost-effectiveness (secondary outcome): Incremental cost-effectiveness ratio will be calculated considering the ratio between the total cost of each treatment and tooth survival after two years.Discomfort reported by the participants (secondary outcome): The data will be summarized as the mean with the standard deviation or the median with the interquartile range, as appropriate. The two groups will be compared after confirming the distribution of data (Normal/non-normal), using the Student's t-test or Mann–Whitney test.Satisfaction of the participants (secondary outcome): The data will be summarized as the mean with the standard deviation or the median with the interquartile range, as appropriate. The two groups will be compared after confirming the distribution of data (Normal/non-normal), using the Student's t-test or Mann–Whitney test.Perception of the Parents/Legal Guardians (secondary outcome): The data will be summarized as the frequencies. The two groups will be compared using the Chi-Square Test.

For all analyzes, the significance value will be set at 5%.

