## Background

Despite the reduction in the prevalence of dental caries, especially in Pediatric Dentistry, caries is still considered a public health problem, since it affects more than 50% of pre-school and school-age children [1]. Data from previous studies also suggest that around 10 to 50% of these children have cavitated lesions on anterior teeth [2–4], which results in negative impact on their quality of life [4]. The evolution of the disease leads to loss of self-esteem, masticatory difficulty, pain, and frustration [4].

Thus, treatments that prevent the progression of these lesions and allow the maintenance of primary teeth until exfoliation while improving the patient's quality of life should be investigated. Restorative techniques are a treatment option for such cavitated lesions [5], but although the available restorative materials have improved, restorations often need replacement, mainly due the patient's failure to control caries risk factors [6].

Since biofilm control is the most critical factor for lesion arrestment, the approach of restoring primary teeth has been questioned [7]. This is corroborated by studies that show that a large part of primary teeth with untreated carious lesions exfoliate without showing any symptoms [8–10].

Therefore, the non-restorative cavity control (NRCC) has been suggested as an option for the treatment of carious lesions in primary teeth. This approach consists of an enlargement of the cavity to allow the adequate removal or disorganization of the daily biofilm through toothbrushing [11–13].

Studies found that this approach shows similar results regarding the improvement of oral-health-related quality of life after one year of treatment [12] and teeth longevity after 3.5 years of follow up [13] compared to conventional composite resin restoration and atraumatic restorative treatment. However, these data come from studies based on posterior teeth restorations [11–13]. Aesthetic is one of the main reasons for replacing restorations in anterior teeth [6], favoring patient engagement for oral care, could also be a stimulus for a frequent brushing of teeth treated with NRCC. However, the acceptability and longevity of this approach has not been compared with the conventional treatment.

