This study aims to evaluate the impact of NRCC for proximal carious lesions in anterior primary teeth on teeth survival. The secondary outcomes will be cost-effectiveness and patients-centered outcomes between the two treatment options. We hypothesize that the survival of teeth treated with NRCC is non-inferior, with a non-inferiority margin of 15%, from that of teeth restored with composite resin.

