## Methods/design

### Study design and ethical aspects

This non-inferiority randomized controlled clinical trial, with two parallel groups with 1:1 allocation ratio was reported according to the Standard Protocol Items for Clinical Trials (SPIRIT) and then registered on the ClinicalTrials.gov platform (NCT03785730). The protocol was approved by the Research Ethics Committee of Universidade Ibirapuera (UNIB). The other centers involved are considered co-participants (Centro Universitário do Norte—Uninorte, Centro Universitário Uninovafapi—UNINOVAFAPI, and School of Dentistry from the University of Sao Paulo—FOUSP).

Children aged 3 to 6 years with at least one proximal cavitated lesion on anterior primary teeth will be selected. Teeth will be randomly allocated to selective removal of carious tissue and resin composite restoration (RCR) or NRCC. Tooth survival after two years of follow-up will be the primary outcome and cost-effectiveness, satisfaction, and discomfort reported by participants and parents/guardians’ perception will be the secondary outcomes.

Only patients who fulfill the eligibility criteria will be included in the study after the legal guardians sign the informed consent form and the child consents to participate in the study.

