### Sample selection

For sample size calculation, we used an expected survival of primary teeth with cavitated lesions in dentin affecting the proximal surface submitted to NRCC of 89.7% after 24 months [13] and a clinically significant difference of 15% in the success rate between groups. Considering a non-inferiority study, a significance level of 0.05 and a power of 0.80, we reached the final number of 102 teeth. Since each child can contribute with more than one tooth, 20% was added to this value (cluster per child), and 20% more was added due to possible sample losses. Thus, the final rounded number of 74 teeth per group was reached, resulting in a total of 148 teeth (sealedenvelope.com).

Children aged 3 to 6 years will be selected from the Clinical Pediatric Research Center—UNIB (CEPECO) (São Paulo, SP, BR), Pediatric Dentistry Clinic—Uninorte (Manaus, AM, BR), Pediatric Dentistry Clinic—UNINOVAFAPI (Teresina, PI, BR) and dental trailer (FOUSP) located on Educational Complex [name] de Lima (Barueri, SP, BR). The screening will be carried out under natural light with the aid of a wooden spatula. Potentially eligible children will be referred for clinical examination.

Recruitment will be taking place from April 2019 to December 2021. After allocation and treatment, the children will be followed up for 24 months. Table 1 displays the flow diagram of the clinical trial phases.

**Table 1 Tab1:** Flow diagram of clinical trial’s phases in according to SPIRIT

Timepoint**	Study period						
	Enrolment	Allocation	Post-allocation				Close-out
	*−t*_*1*_	0	*t*_*1*_	*t*_*2(6 m)*_	*t*_*3(12 m)*_	*t*_*4(18 m)*_	*t*_*5(24 m)*_
*Enrolment*							
Eligibility screen	X						
Informed consent	X						
Allocation		X					
*Interventions*							
NRCC			X				
RCR			X				
*Assessments*							
Survival of tooth				X	X	X	X
Cost-effectiveness			X				X
Discomfort reported by participant			X				
Satisfaction of the participants				X			
Perception of the Parents/legal Guardians		X	X	X			

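### The plan names only an ITT set for a non-inferiority hypothesis and does not settle how an NRCC tooth restored later is counted, so dilution toward non-inferiority could pass unseen

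*Protocol article*

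**What the plan says.** The Protocol article calls itself a non-inferiority trial under Study design and ethical aspects: "This non-inferiority randomized controlled clinical trial, with two parallel groups with 1:1 allocation ratio". The hypothesis at the end of the Background is that survival with NRCC is non-inferior to that with RCR, "with a non-inferiority margin of 15" percent.

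Under Data analysis, the primary outcome is analysed in an ITT population: "The ITT study population will include all randomized participants regardless of protocol deviations". Non-compliance and early withdrawal are treated in the same way. No other population is named. The analyses listed are Kaplan–Meier curves, a log-rank test and a Cox model with shared frailty.

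Under Tooth survival, a tooth is a success if it shows no signs or symptoms of pulp disease, or has exfoliated, and needs no more invasive treatment. Two examples of such treatment follow, a pulp procedure and removal of the tooth, introduced as examples and not as a closed list. The section says what happens to a failed RCR: it is not treated again and the tooth stays under observation. It has no matching statement for an NRCC tooth that is restored during follow-up.

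**The concern.** In a superiority trial, keeping every tooth in its randomised arm is usually the cautious choice. In a non-inferiority trial it need not be, because a tooth that receives the other arm's treatment makes the arms look more alike, and likeness is what the trial hopes to show.

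One such departure can be foreseen. NRCC leaves an enlarged, unrestored cavity in a front tooth for up to 24 months, treatment is unblinded, and parents' view of tooth appearance is itself an outcome. The Background remarks that "Aesthetic is one of the main reasons for replacing restorations in anterior teeth". That sentence is about replacing existing restorations, so it is only indirect support, but it shows that the authors regard appearance as a motive for treating anterior teeth.

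Suppose a family has an NRCC tooth restored, inside or outside the study. The ITT set keeps the tooth in the NRCC arm, and the success definition does not settle its status. If it counts as a success while symptom-free, the NRCC survival estimate partly reflects restoration, and no analysis described in the article would show this.

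**Working it through.** **Inputs from the documents.** Margin 15 points (Background). Allocation 1:1 (Study design and ethical aspects). From Sample selection: expected survival "submitted to NRCC of 89.7% after 24 months", "a significance level of 0.05 and a power of 0.80", and a base size stated as "we reached the final number of 102 teeth".

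**Assumptions.** RCR survival is also taken as 89.7%, since no RCR rate is given. The test is one-sided at 5%; sidedness is not stated. Teeth are treated as independent. The crossover fractions below are assumed.

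**Step 1: reproduce the plan's figure.** With equal survival in both arms,

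n per arm = (1.645 + 0.842)² × 2 × 0.897 × 0.103 / 0.15² ≈ 50.8, rounded up to 51, or 102 in total.

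This matches. One-sided 2.5% would give 65 per arm (130), which does not. The two 20% additions give 102 × 1.2 × 1.2 = 146.9, or 148 as 74 per group. The sample size is not in dispute. It fixes the basis for the next step.

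**Step 2: dilution if restored NRCC teeth are kept and counted by their later course.** Put true NRCC survival at the margin: 0.897 − 0.15 = 0.747. Let a fraction x of NRCC teeth be restored early and then survive like RCR teeth. Then

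- ITT difference d = 0.15 × (1 − x), and NRCC survival p = 0.897 − d
- SE = √{[0.897 × 0.103 + p(1 − p)] / n}
- P(declare non-inferiority) = Φ[(0.15 − d)/SE − 1.645]

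| x (assumed) | d, points | p | SE, n = 51 | False NI, n = 51 | False NI, n = 74 |
|---|---|---|---|---|---|
| 0 | 15.0 | 0.747 | 0.0743 | 5.0% | 5.0% |
| 5% | 14.25 | 0.7545 | 0.0738 | 6.1% | 6.4% |
| 10% | 13.5 | 0.762 | 0.0733 | 7.5% | 8.1% |
| 20% | 12.0 | 0.777 | 0.0722 | 11.0% | 12.6% |
| 30% | 10.5 | 0.792 | 0.0710 | 15.6% | 18.9% |

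Worked line for x = 20%: (0.15 − 0.12)/0.0722 − 1.645 = −1.23, and Φ(−1.23) ≈ 0.11. The 74-per-arm column ignores clustering and losses, which the extra teeth are meant to absorb.

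**Step 3: dependence on the assumed mechanism.** If restoration instead averts 10%, 20% or 30% of NRCC failures, p = 0.747 + c × 0.253 and the difference becomes 12.5, 9.9 or 7.4 points. At 51 per arm, false non-inferiority is then 9.7%, 17.7% or 29.7%. The size turns wholly on inputs that the documents do not give.

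**Step 4: the opposite classification.** If every restored NRCC tooth counts as a failure, NRCC survival at x = 10% is 0.9 × 0.747 = 0.672. The difference is then 22.5 points, against 13.5 in Step 2. The classification rule alone moves the estimate by 9 points and decides the direction of the effect.

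**Step 5: precision of a per-protocol set.** With equal survival and a fraction excluded from both arms, power = Φ[0.15/√(2 × 0.897 × 0.103/n) − 1.645]. At n = 51 it is 80.2%. Excluding 5%, 10% or 20% (assumed) gives 78.3%, 76.4% or 72.0%.

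**The case against.** The strongest reply is that this is a condensed article. Supporting populations and sensitivity analyses are commonly left to a full protocol or analysis plan, which is not shown. A missing per-protocol set would therefore be a weak point on its own. What keeps it alive is that the article does choose and define its analysis set, in terms that retain every deviation, and leaves open an outcome rule on which that choice depends.

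Several stronger readings are tempting and do not stand:

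- *Restored NRCC teeth count as successes.* The article does not say so. The examples of more invasive treatment are open-ended, and a restoration with caries removal, etching and bonding could be held more invasive than enlarging the cavity. It would then be a failure, and the bias would reverse.
- *Deviations will be one-sided.* Nothing in the documents provides for restoring NRCC teeth for appearance. During follow-up, Tooth survival mentions treatment only for pain or a need for more invasive care. The one lasting departure it describes is in the other arm, where failed RCR teeth are left untreated. That is planned policy, not a deviation, and would remain in a per-protocol set.
- *The error rate does exceed 5%.* That needs crossover to occur, to be counted as success and to improve survival. No rate is given for any of these.
- *The non-inferiority conclusion formally rests on ITT.* The log-rank and Cox analyses are not tied to the 15% margin, so the article describes no margin test at all. That is a separate matter; it does not supply a second population.

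The objection also bears on the remedy. Dropping NRCC teeth because they were restored conditions on an event after randomisation in an unblinded trial. If the teeth restored are the worse ones, their removal raises NRCC survival and favours non-inferiority. This stands, and it is why a per-protocol result should support ITT and not be a second condition for success.

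**Conclusion.** The point holds in a limited form. For a non-inferiority hypothesis, the article names only a population that keeps deviating teeth in their randomised arm, and its outcome definition leaves open how an NRCC tooth restored later is counted. Together these allow dilution toward non-inferiority that nothing in the article would detect.

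The size is conditional. The figures of about 7.5%, 11% and 15.6% rest on crossover of 10%, 20% and 30%, a true deficit exactly at the margin, RCR-like survival after restoration, and 51 independent teeth per arm. They show what could happen, not what the plan will produce. ITT is not the wrong primary set, and the sample size is unaffected. The point merits a correction because the event is foreseeable and the remedy is cheap.

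**What to change.** 1. Keep ITT as the primary population.
2. Record at each visit whether an NRCC tooth has been restored since the last one, inside or outside the study, and state in the primary outcome definition whether that is a failure, a censoring event or neither. This concerns how the outcome is counted, not whether such teeth should be restored.
3. Add a per-protocol analysis of the 24-month survival difference against the 15% margin, as a supporting analysis. It would cover eligible teeth that received the allocated treatment and had no later cross-treatment before failure or 24 months. State that disagreement with ITT limits the non-inferiority conclusion.
4. Add a sensitivity analysis in the ITT set that counts any later restoration of an NRCC tooth as a failure. It excludes no tooth, so it avoids the selection problem of the per-protocol set. It is deliberately severe on NRCC and should be read as a bound.

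The cost is one recorded item per visit, a few sentences of definition and two further analyses. The per-protocol set will be less precise (power 76.4% or 72.0% at assumed exclusions of 10% or 20%, against 80.2%) and may carry selection bias. As a supporting analysis it does not require more teeth.

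### The trial is hypothesised and sized for non-inferiority with a 15-point margin, but the stated primary analysis is a log-rank test of equal curves that never uses the margin.

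*Protocol article*

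**What the plan says.** The protocol article commits to non-inferiority in three places.

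- The Background gives the hypothesis that survival with NRCC is "non-inferior, with a non-inferiority margin of 15%, from that of teeth restored with composite resin".
- Study design and ethical aspects labels the trial: "This non-inferiority randomized controlled clinical trial, with two parallel groups with 1:1 allocation ratio".
- Sample selection takes expected survival of teeth "submitted to NRCC of 89.7% after 24 months" and "a clinically significant difference of 15% in the success rate between groups". It then says: "Considering a non-inferiority study, a significance level of 0.05 and a power of 0.80, we reached the final number of 102 teeth". Two 20% additions, for several teeth per child and for losses, bring the total to 148.

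The Data analysis section handles the primary outcome in four steps: a Kaplan-Meier plot in the ITT population, a log-rank test ("The Log-Rank test will be used to compare the survival curves of the two groups"), a shared-frailty Cox model, and hazard ratios with 95% confidence intervals. The Cox model is assigned to the influence of the child's sex and age, the jaw, the tooth type and oral-hygiene habits. Treatment group is not in that list. All tests use 5%, with no side stated. Neither the margin nor the word non-inferiority appears in this section, and the abstract repeats the same Kaplan-Meier, log-rank and Cox plan.

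**The concern.** The log-rank null hypothesis is that the two curves are equal. Rejecting it shows a difference. Not rejecting it shows only that no difference was detected, which with few events is a weak statement. Neither result says whether NRCC is within 15 points of RCR.

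The article therefore has a hypothesis and a sample size on one footing and a named primary test on another. At the end of the trial, either no conclusion on non-inferiority follows from the planned analysis, or a non-significant log-rank is likely to be taken as one. The Discussion says that confirming the hypothesis would support the non-restorative approach, so the rule by which it is confirmed matters.

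**Working it through.** **1. The plan's own figure.** Inputs from Sample selection: survival 89.7%, margin 0.15, significance level 0.05, power 0.80. The article gives 89.7% for NRCC and no figure for RCR. Equal survival in both arms is assumed here.

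n per arm = (z₁₋α + z₀.₈₀)² × 2p(1−p) / margin²

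- One-sided 5%: (1.645 + 0.842)² × 2 × 0.897 × 0.103 / 0.0225 = 50.8, so 51 per arm and 102 teeth. This matches.
- Inflation: 102 × 1.2 × 1.2 = 146.9, so 74 per arm and 148 teeth. This matches.
- One-sided 2.5%: 64.5, so 65 per arm and 130 teeth. This does not match.
- A two-sided superiority formula for 89.7% against 74.7% gives 101 per arm. This does not match.

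The stated number is thus a non-inferiority size at one-sided 5%, on the scale of a difference in 24-month survival.

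**2. The log-rank when NRCC is worse by exactly the margin.** Assume RCR 89.7%, NRCC 74.7%, proportional hazards and independent teeth.

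- Hazard ratio at the margin = ln(0.747)/ln(0.897) = 2.68, and ln(2.68) = 0.987.
- Expected events = n × (0.103 + 0.253).
- Schoenfeld: z = √events × 0.987 / 2, and the chance of a non-significant two-sided 5% test = 1 − Φ(z − 1.96).

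| Teeth per arm | Events | z | Non-significant (Schoenfeld) | Non-significant (simulation) |
|---|---|---|---|---|
| 74, no loss or clustering | 26.3 | 2.53 | 28% | 32% |
| 51 effective | 18.2 | 2.10 | 44% | 48% |

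The 51 effective teeth come from undoing the plan's own allowances: 74 / (1.2 × 1.2) = 51.4. The simulation used 20,000 runs with failures found at 6, 12, 18 and 24 months. A smaller one with exponential failure times (2,000 runs) gave 33% at 74 per arm.

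**3. Range for the unknown RCR survival** (74 per arm, no loss, Schoenfeld).

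| RCR vs NRCC | Hazard ratio | Events | Non-significant |
|---|---|---|---|
| 95% vs 80% | 4.35 | 18.5 | 11% |
| 89.7% vs 74.7% | 2.68 | 26.3 | 28% |
| 85% vs 70% | 2.19 | 33.3 | 38% |

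**4. Whether the hazard ratio could serve instead.** Suppose treatment were added to the Cox model. With equal arms at 89.7%, expected events are 2 × 51 × 0.103 = 10.5, or 2 × 74 × 0.103 = 15.2. At an observed hazard ratio of 1, the upper 95% limit is exp(1.96 × 2/√events) = 3.35 or 2.73. Both exceed 2.68, so even a result of no difference would not clear the margin on that scale.

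**5. A margin-based test on the planned data.** Standard error of the difference at 51 effective teeth per arm = √(2 × 0.897 × 0.103 / 51) = 0.0602, and 0.15/0.0602 = 2.49.

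- One-sided 5% (90% interval): Φ(2.49 − 1.645) = 80%.
- One-sided 2.5% (95% interval): Φ(2.49 − 1.96) = 70%.
- To have 80% with a 95% interval: 65 per arm, times 1.44, gives 94 per arm or 188 teeth.

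**The case against.** The strongest reply is that this is a condensed article and that the exact decision rule may stand in an analysis plan that is not shown. That would answer a complaint about missing detail. It does not answer this point, because the article names its comparative test and that test has a different null hypothesis from the one it states.

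Some stronger readings are tempting, and the documents do not support them.

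- **That the trial cannot answer its question.** It can: Kaplan-Meier estimates to 24 months are planned, and a survival difference with an interval can be taken from them. The defect is in the analysis as written.
- **That the plan has a false-claim rate of 30% or more.** The article nowhere says that a non-significant log-rank will be read as non-inferiority. The rates above describe that misreading, and they also depend on an RCR survival that the article does not give.
- **That it has turned into a superiority trial.** The article does not use that word. Only the null hypothesis of the log-rank is at issue.
- **That an ITT-only analysis is a fault in itself.** The article says "The ITT study population will include all randomized participants regardless of protocol deviations". Deviations can pull arms together, but nothing in the article suggests that crossover is expected, and a supplementary per-protocol set is commonly left to the analysis plan. A set restricted to teeth that kept their allocated treatment could also do harm: failed restorations stay under monitoring, NRCC has no restoration to lose, and the restriction could therefore remove teeth from one arm only.

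**Conclusion.** The point holds. The stated primary analysis does not test the stated primary hypothesis, and this should be corrected before the data are analysed. That conclusion needs no numerical assumption, because it follows from setting the hypothesis and sample size beside the Data analysis section.

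The size of the possible error is conditional. If a non-significant log-rank were taken as non-inferiority, with RCR at 89.7%, NRCC at 74.7% and independent teeth, the claim would be wrong in about 28 to 33% of trials at 74 per arm with full follow-up. It would be wrong in about 44 to 48% at the effective size left after the plan's own allowances. The error rate used for sizing is 5%. For RCR survival from 95% down to 85%, the full follow-up figure runs from about 11% to 38%.

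**What to change.** In Data analysis, and in the abstract's summary of it:

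- Make the primary analysis the difference in 24-month Kaplan-Meier tooth survival, NRCC minus RCR, in the ITT set.
- Use a confidence interval that allows for several teeth per child, for example a robust or bootstrap interval clustered on the child. Sample selection already anticipates this clustering, and a plain log-rank ignores it.
- Declare non-inferiority if the lower limit lies above -15 percentage points.
- State the level. One-sided 5% (a 90% interval) matches the sizing and keeps 80% power at 51 effective teeth per arm. If a 95% interval is preferred, restate the power as about 70%, or plan for 188 teeth under the same allowances.
- Keep the log-rank test and the hazard ratios as supportive.
- Do not make the conclusion depend on a repeat analysis in teeth that kept the allocated treatment.

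With the 90% interval the cost is wording and a clustered interval, with no new data and no change in the number of teeth. With the 95% interval the cost is either lower stated power or 40 more teeth (188 − 148).

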### Sequence generation

Teeth will be randomly assigned into one of the groups considering the strata of the research center (UNIB, FOUSP, Uninorte, and UNINOVAFAPI), in 4, 6, and 8 blocks, according to the sequence obtained by an external examiner generated by the website www.sealedenvelope.com.

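### No cluster-aware estimate of the treatment effect is specified: the arms are compared only by a plain log-rank test, and the shared-frailty Cox model lists neither arm nor centre

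*Protocol article*

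**What the plan says.** **Design.** In the protocol article, Sample selection recognises that teeth of one child are not independent: "Since each child can contribute with more than one tooth, 20% was added to this value (cluster per child"). Sequence generation makes the tooth the unit of allocation and the centre the stratum: "Teeth will be randomly assigned into one of the groups considering the strata of the research center", with four centres and blocks of 4, 6 and 8.

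**Comparison of the arms.** Under Data analysis, apart from Kaplan-Meier curves, one method is named for comparing the arms on the primary outcome: "The Log-Rank test will be used to compare the survival curves of the two groups". Neither stratification by centre nor an allowance for clustering by child is mentioned.

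**Cluster-aware model.** The same section continues: "The multivariate Cox regression with shared frailty model will be used to evaluate the influence of the explanatory variables". The variables given in brackets are sex, age, jaw, type of tooth, toothbrushing, fluoride toothpaste and floss. Arm and centre are absent. The section on data collection and evaluated outcomes also defines the explanatory variables without either.

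**Abstract.** It says that all variables will enter a shared-frailty Cox regression, but names neither arm nor centre.

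**The concern.** The sample size pays for correlation within a child and the randomisation is balanced within centre, yet the stated comparison of the arms uses neither feature. The method suited to correlated teeth is directed at prognostic factors.

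This matters because the trial tests non-inferiority, "with a non-inferiority margin of 15" percent. That conclusion depends on an estimate of the arm effect and the width of its interval. If the standard error is wrong, the interval is wrong with it: too narrow when teeth of one child tend to share an arm, too wide when they tend to be split between arms. If the arm effect is not a stated term of the frailty model, the analyst must decide after the fact which analysis carries the conclusion.

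**Working it through.** **1. The plan's own sample size.** Inputs from Sample selection and Background: survival of 89.7% (taken for both arms), margin 0.15, "a significance level of 0.05 and a power of 0.80, we reached the final number of 102 teeth". Allocation is 1:1.

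- n per arm = (z₀.₉₅ + z₀.₈₀)² × 2p(1−p)/δ² = (1.645 + 0.842)² × 2 × 0.897 × 0.103 / 0.15² = 50.8, so 51 per arm and 102 in all. This matches. One-sided 0.025 would give 65 per arm, 130 in all, so the stated 0.05 is one-sided.
- 51 × 1.2 × 1.2 = 73.44, rounded up to 74 per arm and 148 in all. This matches.

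The design therefore carries a factor of 1.2 for clustering that the stated test does not use.

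**2. If all teeth of a child share an arm.** The true variance is 1 + (m−1)ρ times the naive one, for m teeth per child and correlation ρ. Two teeth with ρ = 0.2 give 1.2, the plan's factor. The actual level of a nominal two-sided 5% test is 2[1 − Φ(1.96/√1.2)] = 7.4%. A nominal one-sided 5% becomes 6.7%.

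**3. If teeth are allocated tooth by tooth, as stated.** When allocation takes no account of the child, the correlation largely cancels and the variance ratio is near 1. When a child's two teeth take neighbouring places in a block of size b, they share an arm with probability (b/2 − 1)/(b − 1), so their arm labels have correlation −1/(b−1): −1/3, −1/5 and −1/7 for b = 4, 6 and 8. With block sizes equally likely, the average over pairs is −(2 × 1/3 + 3 × 1/5 + 4 × 1/7)/9 = −0.204, and the variance ratio is 1 − 0.204ρ:

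- ρ = 0.2: ratio 0.96, two-sided error 2[1 − Φ(1.96/√0.96)] = 4.5%
- ρ = 0.4: ratio 0.92, two-sided error 4.1%

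**4. Simulation under no difference between arms, 148 teeth.** Teeth per child and strength of correlation are assumptions; the documents give neither.

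| Simulated test and setting | Tooth-level allocation | Child's teeth share an arm |
|---|---|---|
| Two proportions, failure 10.3%, 2 teeth, ρ = 0.2, blocks 4/6/8 | variance ratio 0.98, error 5.1% | 1.21, 7.7% |
| Same, 2 teeth, ρ = 0.4 | variance ratio 0.93 | 1.42 |
| Same, 4 teeth, ρ = 0.3 | variance ratio 0.89, error 3.7% | 1.87, 15.6% |
| Log-rank, gamma frailty variance 2 or 6, 2 or 4 teeth | error 4.9% to 5.5% (child ignored), 2.6% to 4.8% (consecutive places in blocks) | error 7.0% to 19.3% |

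Repeat runs of the two-proportion simulation under tooth-level allocation gave variance ratios of 0.87 to 1.03 and errors of 3.2% to 5.8%. At a ratio of 0.87 the naive standard error is 1/√0.87 = 1.07 times the correct one, so 7% too wide. At 1.03 it is 1/√1.03 = 0.985 times, so 1.5% too narrow.

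**5. Events available.** 148 × 0.103 = 15.2 expected failures, or 15.2/4 = 3.8 per centre if spread evenly. Removing the 20% loss allowance leaves 148/1.2 = 123 teeth and 123 × 0.103 = 12.7 failures.

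**The case against.** **The test is close to valid under the stated design.** The Abstract, the study design section and Sequence generation all speak of allocating teeth. The analysis population is described in terms of randomised participants, but that is loose wording and does not say that a child's teeth go to one arm. A reader might infer that the primary test runs at 7.4%, or even 15.6%. Those figures need shared-arm allocation, which the documents nowhere state. This objection stands and sets the size of the point.

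**Clustering is recognised, and the arm may be intended in the model.** A reader might infer that clustering was overlooked or the arm deliberately left out. The documents do not support that either: the sample size and the choice of frailty model both acknowledge clustering, and the Abstract's general phrase could include the arm. The only interval named for the primary outcome, the 95% interval for hazard ratios, follows directly after that model. But the Data analysis section gives an explicit list without arm or centre, and a vague phrase elsewhere does not fill the gap. Nor is this just detail left to a fuller plan, since the article itself fixes the test, the model, its purpose and its variables.

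**The cost of ignoring centre is not quantified.** This stands. The simulations contain no centre effect. Leaving out strata usually costs precision rather than type I error, and how much is unknown here.

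**The two-proportion simulation is not the planned test.** True, but the log-rank simulation shows the same pattern.

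**Conclusion.** The gap in specification is established from the text: the comparison of the arms ignores child and centre, and the one model that handles clustering is not stated to estimate the arm effect.

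Its numerical size is modest. Under tooth-level randomisation, the naive two-sided test is close to nominal or conservative, with error of about 3% to 6% and a variance ratio of about 0.87 to 1.03. The main cost is a mis-stated standard error and some lost precision, not a general excess of false positives. The error rises above nominal only to the extent that teeth of one child share an arm, reaching about 7.4% if all do and the design effect is the plan's 1.2.

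These figures rest on assumed values of 2 to 4 teeth per child and an intra-child correlation of 0.2 to 0.4. The point is worth acting on because the non-inferiority conclusion needs one identified estimate with a correct interval, and that can be specified at almost no cost.

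**What to change.** In the Data analysis section:

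- Name treatment arm as the main term of the Cox model with child-level shared frailty.
- Account for centre with a log-rank test stratified by centre, or with centre as a stratum or covariate in the model if the number of events allows.
- Make the primary estimate the difference in 24-month tooth survival, with a confidence interval that allows for clustering by child (cluster-robust variance or a bootstrap that resamples children), and compare that interval with the 15% margin.
- Keep the plain log-rank test as descriptive.

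The cost is a few sentences and a little programming. The sample size stays at 148 teeth and no new data are needed. The downside is possible instability of the centre terms: with about 15 expected failures over four centres, a baseline hazard stratified by centre together with frailty may not fit reliably. The text should say in advance what replaces the centre terms in that case.
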